#### Response Team Activation

The RRT RN will clinically assess a patient on the inpatient ward if an RRT call is (1) activated traditionally at the clinical discretion of the MRP team or RN or (2) activated by the VSI trigger. Importantly, VSI does not directly lead to clinical decision-making. Clinical decision-making will depend upon the assessment by the practitioners on the RRT.

In this study, the VSI critical threshold is defined as ≥3.0, which is an indication to practitioners of potential deterioration, defined as being a rapid and negative decline in monitored vital signs that require clinical monitoring or intervention. When the VSI reaches ≥ 3.0, the RRT is signaled for activation. This threshold may be changed during the study to balance sensitivity and specificity appropriate to the target population and clinical context. Adjustments will be made based on real-time observations of system performance and clinical relevance, aiming to ensure optimal detection of deterioration while minimizing false alerts. Any changes to the threshold will apply to all enrolled patients to maintain consistency.

The RRT RN will call or visit the ward to discuss the patient’s potential deterioration if a VSI alert is triggered. If erroneous or artefactual data are suspected, the bedside and RRT RNs will troubleshoot the monitoring issue with support from research staff as required. If deterioration is suspected, an RRT member will visit the patient and initiate a formal RRT call if warranted. Patient participation in the study will be complete when continuous monitoring is no longer required, following a minimum of 48 hours and up to a maximum of 10 days. Patients will be followed via their electronic medical records until hospital discharge. Importantly, the maximum monitoring period of 10 days was determined based on the study’s data storage and management capabilities, as this is a pilot study to evaluate the feasibility of using VSI acuity scores. Monitoring duration for each patient will be decided collaboratively by the research team and clinical staff, considering the patient’s clinical condition and study requirements. A future study could evaluate the long-term use of VSI scores beyond this threshold to assess its utility.

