In contrast to relying solely on a single vital sign for cues of deterioration, OBS Medical’s Visensia Safety Index (VSI) is an EWS that uses physiological monitoring software and machine learning to identify the likelihood of deterioration that may lead to cardiac or respiratory arrest [3,5]. As depicted in Figure 1, the VSI is a continuous measure that combines 5 vital signs—heart rate, blood pressure, temperature, oxygen saturation, and respiratory rate—into a single acuity score ranging from 0 (lowest risk) to 5 (highest risk). This score is recalculated in near real-time, with updates occurring at one-minute intervals as new vital sign data are collected. A score of 3.0, or a predetermined threshold determined based on clinical context, or greater represents a critical threshold, suggesting a significant risk of clinical deterioration and prompting an alert to the RRT [4]. The dynamic nature of the VSI allows for continuous monitoring of patient stability and early identification of deterioration trends, enabling timely interventions. Unlike traditional Early Warning Scores, VSI dynamically integrates multiple parameters into a single metric, enabling earlier and more precise detection of deterioration trends. While all five vital signs contribute to the VSI calculation, the system can operate with a minimum of three input parameters, ensuring functionality even when some data are unavailable. This capability makes VSI particularly robust for continuous patient monitoring in dynamic clinical environments.

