#### Data Analysis

Table 3 outlines the statistical analysis that will be conducted to evaluate the study objectives.

The study will collect both quantitative and qualitative data to address its objectives. The results evaluated will include outcomes listed in Textbox 1.

Descriptive statistics will summarize feasibility outcomes. Categorical variables will be presented as counts and percentages, and continuous variables as means and SDs (if normally distributed) or medians and interquartile ranges (if nonnormally distributed).

**Table 3 table3:** Summary of statistical analysis.

Outcome domain	Objective	Statistical analysis
Evaluation	Feasibility	Representation of categorical variables as counts and percentages. Representation of continuous variables with either (1) means with SDs if a normal distribution is followed, or (2) medians with interquartile ranges if a non-normal distribution is followed.
Evaluation	Clinical impressions	Interview transcripts will be examined to identify barriers and enablers for the implementation of a VSI^a^ trigger using content-directed coding into CFIR^b^ constructs [8,9]. Additional inductive analysis of quotations within CFIR constructs for interpretation, with themes being periodically examined for revision, combination, and deletion as needed [12]. All transcripts will be double coded by 2 independent researchers meeting for consensus regularly.
Impressions	Clinical impact	Calculation of sensitivity and specificity with respect to the ability of the VSI score to predict intensive care unit admissions. Analysis of practitioner’s initial impressions of the system as well as challenges and benefits to its use.

^a^VSI: Visensia safety index.

^b^CFIR: Consolidated Framework for Implementation Research.

Feasibility outcomes.

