### Predictive Performance

The predictive performance of the VSI-triggered alerts will be compared to clinical gestalt using sensitivity, specificity, positive predictive value, and negative predictive value. Quantitative data will be analyzed using statistical software, and subgroup analyses will account for variability across patient populations and clinical settings [21].

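### If the alert threshold is changed on study performance, VSI accuracy becomes either a mixture over thresholds or optimistic, because no analysis threshold is fixed

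*Protocol article*

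**What the plan says.** All references are to the protocol article.

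- **Starting value** (Response Team Activation): "In this study, the VSI critical threshold is defined as ≥3.0".
- **Permission to move it** (same section): "This threshold may be changed during the study to balance sensitivity and specificity appropriate to the target population and clinical context". The basis is given as: "Adjustments will be made based on real-time observations of system performance and clinical relevance". The article gives no rule for when, how often or by how much.
- **Scope of a change** (same section): "Any changes to the threshold will apply to all enrolled patients to maintain consistency". It does not say whether monitoring time already completed is re-scored, or whether only alerts from that point on are affected.
- **Accuracy against gestalt** (Predictive Performance): "The predictive performance of the VSI-triggered alerts will be compared to clinical gestalt using sensitivity, specificity, positive predictive value, and negative predictive value".
- **Accuracy for ICU admission** (Data Analysis, Table 3): "Calculation of sensitivity and specificity with respect to the ability of the VSI score to predict intensive care unit admissions".

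Neither accuracy statement names a cut-off. Both draw on the single cohort of 70 in the Sample Size section, and no separate validation set is described. The title of Table 1 places clinical impact, which includes these accuracy measures, among the primary objectives. Alert frequency is a listed feasibility outcome. Criterion (d) in Table 1 is the share of triggers reported to the RRT.

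**The concern.** The threshold is part of the definition of the test under evaluation. The plan allows that definition to move in response to how the test performs in the study. The stated aim of a move is to alter the balance of sensitivity and specificity, which are the quantities then reported from the same patients. With no analysis threshold fixed, two readings of the plan are open after a change, and each gives a poor estimate in its own way. Applying a change to everyone enrolled keeps practice uniform at any one time. It does not keep the definition constant across the study.

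At stake are the comparison of VSI with gestalt and the use of the accuracy figures in designing later interventional trials, which the Conclusion names as a purpose. Alert frequency and the denominator of criterion (d) also shift with the threshold, so their totals would combine periods that are not alike.

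**Working it through.** **1. What the plan's own figures allow.** The article states no sensitivity, specificity, event rate or precision target. Its only relevant number is 70 patients, a convenience sample. Ten months is 10 × 365.25 / 12 / 7 = 43.5 weeks. At 1 to 2 patients per week overall this gives 43 to 87, so 70 (1.61 per week) fits. No formula yields it. Everything below therefore needs assumed inputs.

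**2. Assumed inputs (not in the article).** One normally distributed peak score per patient with SD 0.8; ICU admission rate 10, 20 or 30%; AUC 0.70 or 0.80; specificity at 3.0 of 0.60 or 0.80; retuning by maximum sensitivity + specificity on a 0.1 grid from 1.5 to 4.5; N = 70; up to 6,000 runs in each of the 12 scenarios.

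**3. Measure.** Optimism = apparent (sensitivity + specificity) − true (sensitivity + specificity) at the threshold or thresholds actually used.

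**4. Results (range over the 12 scenarios).**

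| Reading of the plan | Optimism | Thresholds in the estimate |
|---|---|---|
| Never changed, 3.0 throughout | −0.003 to +0.004 | one |
| Alerts as fired: first 35 at 3.0, next 35 at the value tuned on the first 35 | −0.003 to +0.003 | two |
| Tuned on first 35, all 70 re-scored at that value | 0.07 to 0.13 | one |
| Tuned on all 70, same 70 scored | 0.10 to 0.19 | one |

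In the last row the excess is mostly in sensitivity (7 to 18 points) rather than specificity (1 to 3 points), because there are few events.

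In the second row optimism vanishes because later patients are judged at a threshold set before their data existed. The cost is that the two thresholds being mixed differ on average by 13 to 21 points in true sensitivity and 12 to 19 points in true specificity.

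**5. A worked mixture.** Assume normal scores, SD 0.8, non-event mean 2.4 and AUC 0.75. The event mean is 2.4 + 0.8 × √2 × Φ⁻¹(0.75) = 2.4 + 0.8 × 0.954 = 3.16. Sensitivity at cut c is Φ((3.16 − c)/0.8) and specificity is Φ((c − 2.4)/0.8):

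| Cut | Sensitivity | Specificity |
|---|---|---|
| 2.5 | 80% | 55% |
| 3.0 | 58% | 77% |
| 3.5 | 34% | 92% |

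If half the events and half the non-events were scored at 3.0 and half at 2.5, the pooled sensitivity would be (58 + 80)/2 = 69% and the pooled specificity (77 + 55)/2 = 66%. Neither figure describes either threshold, and both depend on when the change happened to fall.

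**6. After the fix.** Scoring all 70 at 3.0 is the first row of the results table: optimism about zero and one threshold. It does not cure imprecision. With about 80% observed sensitivity, the exact (Clopper-Pearson) 95% intervals are 42–100% for 6/7, 49–95% for 11/14 and 58–95% for 17/21, for assumed ICU admission rates of 10, 20 and 30%.

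**The case against.** **The change is permitted, not planned.** This stands. If the option was never used, no bias and no mixing arise.

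**Optimism and mixing are largely alternatives.** This stands. A reader might infer that the accuracy figures will be both inflated and tied to no single threshold. The calculation does not support that: alerts counted as fired show essentially no optimism, and re-scoring at a tuned value restores a single threshold. The article does not say which reading applies. The Predictive Performance section speaks of alerts, which points to the mixture. Table 3 speaks of the score, and the sentence extending changes to all enrolled patients could be read as re-scoring. It would also be inference to say that the article prescribes pooling across a change.

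**The simulation models formal tuning.** This stands. The text describes real-time observation of performance and clinical relevance, not maximising an index over completed outcomes. Informal adjustment would probably give less optimism.

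**A contradiction with the Introduction.** A reader might set "A score of 3.0, or a predetermined threshold determined based on clinical context, or greater represents a critical threshold" against the permission to change the threshold. The Introduction describes the product in general, while the study rule is in Response Team Activation. This is not a contradiction.

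**Detail belongs in an analysis plan.** This holds in part. ROC curves and correction methods are ordinary analysis-plan content, and their absence is no finding. What remains is that the protocol itself authorises a performance-driven change in the test definition and fixes no cut-off for the accuracy analysis.

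**Feasibility is unaffected.** This holds for the 80% technical criterion, which uses neither sensitivity nor specificity. Only the trigger count behind criterion (d) depends on the threshold.

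**Conclusion.** The point holds conditionally. If the threshold was changed on observed performance, the reported accuracy will be one of two things:

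- a mixture over thresholds, with little optimism but component sensitivities about 13 to 21 points apart; or
- optimistic, by about 0.07 to 0.19 on sensitivity plus specificity.

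The plan does not say which. These sizes rest on the assumed admission rates, AUC, score distribution, half-way change point (for the mixture and the 0.07 to 0.13 part of the range) and formal tuning, so they indicate scale and are not forecasts. Nothing elsewhere in the article removes the ambiguity. The conclusion on technical feasibility does not turn on it. The comparison with gestalt, and any accuracy figure carried into a later trial, does.

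**What to change.** Separate the operating threshold from the analysis threshold:

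1. State that primary sensitivity, specificity, PPV and NPV are computed at the pre-stated VSI ≥ 3.0 for every patient, whatever threshold was live. Use the minute-level data described under Data Management. That section confirms stored vital signs but not stored scores, so the score may have to be recomputed.
2. Log the date and reason of each threshold change. If there was none, say so; the issue then closes.
3. Report alert frequency, RRT activations and criterion (d) by threshold period.
4. Label accuracy at any retuned cut as exploratory and derived in this sample, with a bootstrap or cross-validation correction for optimism.

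**Cost.** Analysis wording, plus possible recomputation of scores. The article reports enrolment complete and analysis ongoing as of April 2025, so on that status the change needs no new data. Headline accuracy may be slightly less favourable. Re-scoring cannot undo the fact that patients were managed under the live threshold: alerts prompt RRT assessment, which could affect ICU admission. That should be stated as a limitation. The change concerns the analysis cut-off only. It leaves the operational freedom to adjust alerts untouched and takes no view on which bedside threshold is right.

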#### Interviews

Incorporating a portable continuous monitoring system with a VSI trigger into practice constitutes a complex intervention [7,9]. Therefore, we will conduct postimplementation semistructured interviews with involved physicians, RNs, and research personnel members of the RRT and wards where the portable continuous monitoring with VSI trigger is implemented. Importantly, despite not being part of the clinical team, research personnel were involved in setting up the study, including backend management of the VSI acuity score generation and ensuring proper functionality of the monitoring systems used in the study. Their expertise with the technical aspects of the VSI system and its integration into workflows makes their insights valuable in evaluating the ease of implementation and identifying potential barriers or enablers. Including them in interviews allows for a comprehensive assessment of the implementation process from both technical and clinical perspectives.

Interviews will be 30 to 45 minutes in anticipated length and structured using the Consolidated Framework for Implementation Research (CFIR) [16-18]. This framework describes the range of the barriers and drivers to the effective implementation of complex interventions at multiple levels and among many stakeholders; it has been used in health care settings to evaluate the implementation of innovations [17,19,20]. We will select CFIR constructs relevant to the current implementation collaboratively with the research team. We will develop questions relevant to each selected construct to explore the range of barriers and drivers to using the Masimo monitoring and VSI trigger–induced alerts and evaluate health care providers’ intentions to use such EWS in clinical practice. The guide will be pilot-tested for length, clarity, and comprehensiveness and revised as needed.

Potential interviewees will be identified by the research team and emailed an initial invitation and consent form to participate, with up to 2 email reminders. Verbal consent will be obtained at the time of the interview. Interviews will be divided into 2 sections. Section 1 will include background and demographic questions. Section 2 will assess potential barriers and drivers to using the monitoring and alerts according to the CFIR, with particular attention to (1) questions about the monitoring itself and how it compares to current processes, (2) environmental issues around resources and the setting in which the monitoring is being used, (3) the individuals involved in the implementation and other colleagues that may assist with or impede use, and (4) the implementation process itself including the implementation context and the adaptability of the innovation and setting. We will also ask about goals for use, and beliefs about outcomes related to monitoring use (see Multimedia Appendix 1 for the full interview guide including related CFIR constructs). Interviews will be audiotaped and transcribed, and field notes taken during the interview. All physicians, RNs, and research personnel who participate in an interview will receive a token of appreciation for their time and expertise.

### Sample Size

The sample size is based on a convenience sample obtainable with the currently available resources. The target feasibility metrics for this study are depicted in Table 1. Projected enrollment is 1-2 new patients per week at both centers for a total of 70 patients over a 10-month period. The sample size of 70 patients was selected to ensure sufficient variability in patient characteristics and clinical scenarios to evaluate feasibility outcomes, including the proportion of continuous data successfully collected and transmitted, VSI alert timeliness, and completion rates of study-related tasks.

Approximately 10-15 physicians, and 10-15 nurses, from both the RRT and ward will be interviewed alongside 2-4 research personnel who are involved in the care of patients enrolled in the clinical implementation portion of this study. Purposive sampling will include consideration of all patient subgroups listed in the inclusion criteria to ensure respondents are from a variety of clinical backgrounds. The interview sample size estimates are based on previous work around theme saturation using theory-informed interviews [21].

### Data Management

The output of VSI is comprised of two components: (1) the first produces a real-time risk score based on the patient’s own vital signs to ultimately send alerts to clinicians and (2) a user interface with all patients and their acuity continuously displayed and updated. The system has current US Food and Drug Administration (FDA) and Conformité Européenne (CE) clearance.

The VSI is a software application consisting of both a software backend hosted on a hospital server and a front-end dashboard accessible via a web browser. It is backed by two databases: a low-volume database storing the configuration information and a high-volume database storing anonymized vital sign information. Data are fed into the VSP by means of Health Level 7 (HL7), version 2. Feeds communicated once every minute provide a good balance between data storage requirements and data usefulness. They will be correlated to the same anonymous identification number as the vital sign data.

Several options exist for the anonymization of HL7 data from patients, depending on the hospital infrastructure. In this study, the anonymization will be performed on the VSP server via the installation of Mirth Connect before sending the data to the VSP. The VSP’s own database (anonymized vital signs) would be accessible by the sponsor (for study management purposes); however, the mapping table between study IDs and Protected Health Information/Personally Identifiable Information would only be accessible by the study data custodian.

#### Safety Reporting

Any safety issues related to the VSI will be addressed by the study co-principal investigators and study sponsor, OBS Medical. RRT RNs and physicians can bring any safety concerns to the RRT leads, who will communicate these to the study co–principal investigators. Concerns will be discussed and addressed on the same day. All safety issues will also be communicated to OBS Medical. Clinical issues will be addressed by the study co–principal investigators and technical issues will be addressed by OBS Medical. All safety issues will additionally be reviewed during the next monthly steering committee meeting.

All adverse device effects need to be assessed by the site investigator for severity, seriousness, expectedness, and causality/relatedness. The site investigator is required to report serious adverse events or serious adverse device effects to Health Canada and the Regulatory Correspondent within 72 hours of discovery. This includes cases in which the incident relates to the improper functioning or failure of the device or serious deterioration or death of the patient participant. It is expected that any serious untoward medical occurrence, unintended disease or injury, or untoward clinical signs (including abnormal laboratory findings) in subjects, users, or other persons, whether related to the investigational medical device, will be reported.

#### Study Management

A steering committee comprised of all investigators will meet monthly to discuss the study’s progress. This committee includes representatives from TOH leaders from information services, biomedical engineering, research coordinators, and investigators. Concerns raised by any staff will be evaluated monthly to guide changes to the protocol in an ongoing fashion. Interim results from interviews will be reviewed at every second meeting.

#### Data Analysis

Table 3 outlines the statistical analysis that will be conducted to evaluate the study objectives.

The study will collect both quantitative and qualitative data to address its objectives. The results evaluated will include outcomes listed in Textbox 1.

Descriptive statistics will summarize feasibility outcomes. Categorical variables will be presented as counts and percentages, and continuous variables as means and SDs (if normally distributed) or medians and interquartile ranges (if nonnormally distributed).

**Table 3 table3:** Summary of statistical analysis.

Outcome domain	Objective	Statistical analysis
Evaluation	Feasibility	Representation of categorical variables as counts and percentages. Representation of continuous variables with either (1) means with SDs if a normal distribution is followed, or (2) medians with interquartile ranges if a non-normal distribution is followed.
Evaluation	Clinical impressions	Interview transcripts will be examined to identify barriers and enablers for the implementation of a VSI^a^ trigger using content-directed coding into CFIR^b^ constructs [8,9]. Additional inductive analysis of quotations within CFIR constructs for interpretation, with themes being periodically examined for revision, combination, and deletion as needed [12]. All transcripts will be double coded by 2 independent researchers meeting for consensus regularly.
Impressions	Clinical impact	Calculation of sensitivity and specificity with respect to the ability of the VSI score to predict intensive care unit admissions. Analysis of practitioner’s initial impressions of the system as well as challenges and benefits to its use.

^a^VSI: Visensia safety index.

^b^CFIR: Consolidated Framework for Implementation Research.

Feasibility outcomes.

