**Figure 1 figure1:**
[figure not shown]
An infographic showing the patient setup for this study. Image created on BioRender. SpO2: oxygen saturation; VSI: Visensia Safety Index.

A retrospective cohort study of 168 patients found that 95% of the episodes of severe physiological abnormalities were identified by the VSI system and deemed valid, defined as requiring a change in clinical management [12]. A 3-phase prospective study was implemented for validation at the University of Pittsburgh Medical Centre, which included a continuous collection of cardiorespiratory variables in a non-ICU patient population [13]. Patients monitored with VSI had a statistically significant shorter average duration of any instability, shorter average duration of physiological instability, and fewer episodes of serious and persistent instability [13]. While continuous monitoring likely contributes to these outcomes, the VSI integrates multiple physiological parameters into a single predictive score, enabling earlier identification of deterioration trends compared to traditional EWS. By providing a more comprehensive and dynamic view of patient stability, VSI facilitates timely clinical interventions that may not occur with traditional monitoring systems alone [4].

A recent retrospective cohort study at The Ottawa Hospital (TOH) compared outcomes for patients who would have had an EWS alert, triggered by VSI or the National Early Warning Systems 2 (NEWS2), prior to RRT activation to patients without an EWS alert [14]. It was found that an EWS would have identified earlier deterioration for over half of the patients; however, clinical impact requires interventional study. While both the VSI and NEWS2 may have contributed to the favorable findings of early deterioration detection, EWS like NEWS2 have limitations in sensitivities, underscoring the need for more dynamic tools like VSI to improve early detection in real-world settings [5,15].

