#### Patient and Study Team Timeline

Once the patient is on continuous monitoring, the following will be completed on a daily basis:

The patient is clinically assessed in person by the RRT, as per the standard of care for patients on the RRT roster. These assessments will include a clinical evaluation of the patient’s condition, a review of vital sign trends, and any alerts generated by the VSI.The RRT RN completes the Daily RRT visit log to capture the opinion of deterioration risk for the ward and RRT staff and the status of VSI monitoring. This includes the nurse’s assessment of the patient’s risk of deterioration based on clinical judgment, observations of vital sign trends, and any relevant changes in the patient’s condition.The RRT RN completes the RRT event log for any calls to the RRT for patients.The research coordinator completes the patient’s case report form, capturing demographic data as well as any deterioration events and outcomes.

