**Feasibility outcomes**
The proportion of continuous data successfully collected, transmitted, and analyzed using the Visensia Safety Index (VSI) system.The frequency and timeliness of VSI-triggered alerts and rapid response team activations.Completion rates for study-related tasks, including data logging, daily assessments, and interviews.Technical barriers encountered during system implementation and integration.

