**Conclusion**

This study protocol outlines a mixed methods approach to evaluate the feasibility and clinical impressions of integrating continuous VSM with the VSI for early detection of patient deterioration and rapid response team activation. By combining prospective data collection with theory-informed qualitative interviews, this study aims to identify key implementation barriers and enablers within real-world hospital workflows. Findings from this feasibility study will inform the design of future interventional trials and guide the broader integration of predictive monitoring systems into acute care settings.

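### VSI sensitivity is scored against ICU admission with no requirement that the alert precede a ward-initiated RRT call, so it cannot by itself be read as early detection

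*Protocol article*

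**What the plan says.** **Reference event.** Under Data Analysis, the clinical impact row of Table 3 plans "Calculation of sensitivity and specificity with respect to the ability of the VSI score to predict intensive care unit admissions". The Predictive Performance section adds: "The predictive performance of the VSI-triggered alerts will be compared to clinical gestalt using sensitivity, specificity, positive predictive value, and negative predictive value". Neither that section nor Table 1 names another reference event, and no section says when an alert must occur in order to count.

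**Routes to a call.** Under Response Team Activation, an RRT call may be "activated traditionally at the clinical discretion of the MRP team or RN or (2) activated by the VSI trigger". A ward call can therefore come before any alert.

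**Clinical gestalt.** Table 1 says clinical impact will be assessed with the patient acuity rating. Under Patient and Study Team Timeline, a daily visit log records ward and RRT staff opinion of deterioration risk.

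**Purpose.** The Conclusion describes the study as one of "integrating continuous VSM with the VSI for early detection of patient deterioration and rapid response team activation". The Introduction and the Discussion overview also present earlier detection as the expected benefit.

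**Timing.** The feasibility outcomes list "The frequency and timeliness of VSI-triggered alerts and rapid response team activations". Nothing links this outcome to the sensitivity calculation.

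**The concern.** ICU admission lies downstream of clinician detection. If the ward team calls first, the patient may stay connected to the monitor while the RRT assesses and until transfer; no section stops monitoring or scoring at the call. A VSI that first crosses its threshold in that interval precedes the ICU admission, and so meets Table 3 as worded, although clinicians had already recognised the deterioration.

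Two readings of the result are then at risk. First, a sensitivity that includes such alerts could be taken as evidence that the VSI detects deterioration early. Second, the comparison with gestalt could be uneven. If the daily log supplies the gestalt rating, clinicians are scored on one judgement a day, while the VSI is scored on values updated every minute, possibly up to transfer. Take a patient rated low risk in the morning, for whom the ward calls the RRT in the afternoon and the first alert comes minutes later. That patient would count as a VSI success and a gestalt failure, although ward staff acted first.

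**Working it through.** **Inputs from the article**
- Reference event: ICU admission (Table 3).
- Order of call and alert: either may come first (Response Team Activation).
- Sample: 70 patients, a convenience sample (Sample Size).
- Not given: an expected sensitivity, an ICU admission rate, or the share of alerts that follow a ward call. There is no planned figure to reproduce.

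**Definitions**
- N: ICU admissions.
- A: admissions with a first alert at any time before admission.
- L: the subset of A whose first alert falls between a ward-initiated RRT call and admission.
- Form (a), any alert before admission: Se(a) = A / N.
- Form (b), first alert before the first RRT call not triggered by the VSI, or before admission where there was no such call: Se(b) = (A − L) / N.

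**Direction**

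Se(a) − Se(b) = L / N, which is never negative. It is zero if L = 0 and positive if even one admission has a late first alert.

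**Illustration (assumed: 15% ICU admission rate, Se(a) of 80%)**

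15% of 70 is 10.5, taken as N = 10, with A = 8. Intervals are exact (Clopper-Pearson) 95%.

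| Late alerts L | Se(b) | 95% CI |
|---|---|---|
| 0 | 8/10 = 80% | 44% to 97% |
| 1 | 7/10 = 70% | 35% to 93% |
| 2 | 6/10 = 60% | 26% to 88% |
| 4 | 4/10 = 40% | 12% to 74% |

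In terms of the late share s = L / A, Se(b) = Se(a) × (1 − s). With Se(a) = 80%, this gives 0.80 × 0.90 = 72% at s = 10%, 0.80 × 0.75 = 60% at 25%, and 0.80 × 0.50 = 40% at 50%. Over late shares of 0 to 50%, the gap runs from 0 to 40 points.

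**Sensitivity to the assumed event rate**

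ICU admission rates of 5% to 30% give about 4 to 21 events among 70 patients. One late alert then moves sensitivity by between 1/4 = 25 points and 1/21 = about 5 points. With so few events, the classification of one or two patients is visible in the result, although the intervals are wide under either form.

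**The case against.** **The counting rule may exist elsewhere.** A reader might infer that the plan definitely counts late alerts as correct predictions. The article does not say so. It neither includes nor excludes them, and a full protocol or analysis plan, not shown, may settle the matter. This stands. What the article does fix is the reference event, and on its plain wording a late alert qualifies.

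**The figure is right for what it names.** As sensitivity for ICU admission, an alert before admission is a legitimate true positive, and timeliness is a separate outcome. This also stands: the figure overstates only if read as early detection. But that is the stated purpose, and a separate descriptive timing summary does not show which true positives were early.

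**No size can be taken from the earlier hospital study.** The Introduction describes a retrospective study at the same hospital that compared patients who would have alerted "prior to RRT activation to patients without an EWS alert", and found earlier identification for more than half. A reader might infer that up to nearly half of ICU-bound patients have no alert before the call, and so that the planned sensitivity would approach 100% and run 30 to 50 points too high. The article does not support this. That result concerns VSI or NEWS2 alerts, in RRT patients rather than ICU admissions, and no source says how many of the rest would cross the threshold after the call. The study does show that timing relative to RRT activation is a meaningful reference.

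**Gestalt is a rating, not the call.** The comparator is a recorded judgement of risk, so it would be wrong to say that it found the late-alert cases first. The narrower point remains: a daily rating and a minute-by-minute score do not have equal opportunity to be right.

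**Counting late alerts as misses has its own bias.** Under Anticipated Strengths and Limitations, ward staff can view the dashboard. A nurse who sees a rising score and calls before it reaches the threshold would turn that case into a VSI miss under form (b). This stands, and is why both forms should be shown.

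**Admissions after monitoring ends.** Monitoring lasts at most 10 days, while follow-up runs to discharge. Counting later ICU admissions would lower sensitivity in both forms, so the net error in the reported figure is unsettled. It does not make a late alert early.

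**Conclusion.** The point holds in a limited form. Table 3 scores the VSI against ICU admission without requiring the alert to precede a ward-initiated RRT call, and the article allows such calls to come first. Unless late alerts are separated out, sensitivity cannot be read as early detection, and the comparison with a once-daily rating may favour the VSI.

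The direction follows from the definitions: form (a) is never below form (b). The size is unknown and may be zero; the figures above rest on an assumed ICU admission rate, any-time sensitivity and late share. The mechanism also assumes that monitoring continues after the ward call. The documents do not support saying that sensitivity for ICU admission itself is inflated.

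Severity is minor. This is a feasibility study whose success criteria in Table 1 are the 80% technical targets, which this point does not touch.

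**What to change.** In the clinical impact row of Table 3, report sensitivity for ICU admission in two forms side by side:

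- (a) first alert at any time before ICU admission;
- (b) first alert before the first RRT call not triggered by the VSI, or before ICU admission where there was no such call.

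Report the alert-to-call lead time with them. Base any early-detection claim and the comparison with gestalt on (b). State that ward staff could see the VSI dashboard, which may have moved calls earlier.

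The minute-by-minute feed described under Data Management gives the alert times. For the calls, the article says "The RRT RN completes the RRT event log for any calls to the RRT for patients"; the ordering can be done if that log records call times.

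The cost is a little more analysis work and a sensitivity for early detection that may be less favourable. The Results section reported analysis still under way in April 2025. If results have since been finalised, the split can be added as a labelled supplementary analysis.
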